#### Assumption checking

The Cox regression model assumption of proportional hazards will be examined in two ways: (i) firstly, through graphical review of the survival curves – if the survival curves are observed to cross this would indicate non-proportionality; (ii) through inclusion of a time-arm interaction in the regression model with statistical significance of this term signifying important deviation from the assumption of proportional hazards. If either of the two examinations shows violation of the proportional hazards assumption then alternative statistical testing will be performed using an unadjusted log rank test.

For the linear models we will examine inverse normal plots to check for normality (in the event of any reasonable violation we will use a suitable data-transformation function). Potential covariance structures will be explored for goodness-of-fit of mixed models through comparing likelihood and Bayesian Information Criteria (BIC).

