### Clinical outcomes analysis

#### Primary analysis

The primary analysis will compare time to self-reported resolution between stratified care and non-stratified care, on an intention-to-treat basis. A Kaplan-Meier survival analysis will estimate the time from randomisation until first resolution of symptoms. Participants who drop out of the trial through active withdrawal will be censored at the time this occurs (by contrast, participants not responding at any time point will continue to be followed-up until they actively withdraw). This will provide the data for comparing the relative mean and median survival times of the two trial arms. A Cox proportional hazards regression analysis will compare time to resolution between arms by calculation of a hazard ratio (HR) of rates of resolution adjusted for centre, patient stratification group (subgroups: 1, 2, 3) and baseline pain duration. The HR will be presented along with a 95% confidence interval for the HR; a p-value < 0.05 (two-tailed) based on the Wald test statistic will signify rejection of the null hypothesis of no difference in recovery time between the two arms. A statistically significant p-value with HR > 1 would indicate statistically significant shorter time to recovery for stratified care compared to control; a statistically significant p-value with HR < 1 would indicate a (statistical) significantly longer time to recovery for stratified care compared to control. The analysis will account for physiotherapist effect (proportional Cox hazards frailty model).

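### Any crossing of the survival curves moves testing to an unadjusted log-rank test, yet crossing is mostly chance and the log-rank test does not remedy non-proportional hazards

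*Protocol article*

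**What the plan says.** Primary analysis sets the confirmatory test. The hazard ratio is "adjusted for centre, patient stratification group (subgroups: 1, 2, 3) and baseline pain duration", the null is rejected on "a p-value < 0.05 (two-tailed) based on the Wald test statistic", and a further sentence adds clustering: "The analysis will account for physiotherapist effect (proportional Cox hazards frailty model").

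Assumption checking then gives two checks of proportional hazards. The first is a look at the plotted curves: "if the survival curves are observed to cross this would indicate non-proportionality". No size, timing or significance threshold for a crossing is given. The second works "through inclusion of a time-arm interaction in the regression model with statistical significance of this term". One positive check is enough, since the condition reads "If either of the two examinations shows violation of the proportional hazards assumption". The stated consequence of meeting it is that "alternative statistical testing will be performed using an unadjusted log rank test". The rule names no effect estimate to go with that test.

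Blinding and protection against bias states that no physiotherapist treating stratified-care patients treats control patients, so physiotherapists are nested within arm. Sample size allows for a physiotherapist ICC of up to 0.01 and a coefficient of variation in cluster size of 0.65.

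**The concern.** The rule lets the data choose the test, and it has three weaknesses.

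1. **The trigger.** Two estimated curves that share the same true curve interleave by chance. Crossing is then a sign that the arms are close, not that the hazard ratio changes over time. The switch would therefore fire most often when there is no effect, which is where type I error is defined.
2. **The destination.** The log-rank test is the score test of the Cox model without covariates. Moving to it leaves any non-proportionality where it was, and the reader loses the hazard ratio and its interval.
3. **What is dropped.** The fallback leaves out the stratification factors, pain duration and the physiotherapist frailty. With physiotherapists nested in arm, ignoring clustering makes the test anti-conservative.

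At stake are the level of the confirmatory test, some power, and clarity about which p-value decides the trial.

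**Working it through.** **Inputs from the protocol article.** 470 participants, 235 per arm, 1:1; 20% dropout, so 470 × 0.8 = 376 effective; two-sided 5%; HR 1.4 at 90% power (all resolved by 12 months, ICC below 0.001) or HR 1.5 at 80% power (60-65% resolved, ICC 0.01); cluster-size CV 0.65; readings weekly for 4 months (16), then 4-weekly to 12 months (9). Mean cluster size is not stated.

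**Step 1: reproduce 470.** Schoenfeld events = 4(z₀.₉₇₅ + z_power)² / (ln HR)².
- HR 1.4, 90%: 372 events; 372 / 0.8 = 465.
- HR 1.5, 80%: 191 events. Design effect DE = 1 + ((1 + CV²)m − 1) × ICC, with 1 + 0.65² = 1.4225.
  - 60% resolved, m = 13: DE = 1 + (18.49 − 1) × 0.01 = 1.175; 191 / 0.60 × 1.175 / 0.8 = 468.
  - 65% resolved, m = 20: DE = 1 + (28.45 − 1) × 0.01 = 1.274; 191 / 0.65 × 1.274 / 0.8 = 469 after rounding up.

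So 470 is consistent with a mean cluster size of about 13-20. That range is inferred.

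**Step 2: how often the trigger fires when hazards are exactly proportional.** 4,000 simulated trials per setting; 235 per arm; the reading schedule above; 20% uniform dropout; constant or Weibull (shape 0.7) hazards. A crossing is any sign change in the Kaplan-Meier difference. Ranges cover the settings in each row.

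| True HR | Resolved at 52 weeks | Any crossing | Crossing over 2 points each side | Time-by-arm p < 0.05 | Either trigger |
|---|---|---|---|---|---|
| 1.0 | 60-65% | 78-87% | 44-50% | 4-5% | 79-87% |
| 1.0 | 97% | 88-93% | 55-62% | 3-4% | 88-93% |
| 1.4 | 60-65% | 27-49% | 8-12% | 4-5% | 29-52% |
| 1.5 | 60-65% | 19-42% | 4-8% | 4-5% | 21-44% |
| 1.4-1.5 | 97% | 4-26% | 1-7% | 2-3% | 6-28% |

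Other runs with somewhat different event-rate and dropout settings gave 74-87% crossing at HR 1.0, and as little as 17% at HR 1.4-1.5. The time-by-arm term alone fires at about its nominal rate; nearly all false alarms come from the crossing rule.

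**Step 3: does the fallback help?** Log-rank and unadjusted Cox Wald z statistics correlated at 0.99998. Without clustering, the log-rank test rejected a true null in about 5% of trials, so its level is sound. With hazards that truly cross (HR 1.6 to week 12, then 0.6), log-rank rejected in 6-7% and covariate-adjusted Cox in 5-6%: neither has useful power.

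**Step 4: cost of dropping the clustering.** If an unclustered log-rank test were always used, type I error = 2(1 − Φ(1.96/√DE)).
- ICC 0.01: DE 1.175 gives 7.1%; DE 1.274 gives 8.3%.
- ICC 0.001: m = 13 gives DE 1.017 and 5.2%; m = 20 gives DE 1.027 and 5.3%.

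The plan uses the log-rank test only after a trigger, and curves that cross tend to be close. A simulation of the two-stage rule (6,000 trials per setting, HR 1, 62% resolved, frailty variance 0.0166 assumed for ICC 0.01) gave, at DE about 1.22, 7.6% for always-log-rank but 5.8% (Weibull) to 6.6% (constant hazard) for the rule. At DE 1.31-1.32 the rule gave 6.4-6.7%. Among trials with a crossing, log-rank rejected in 3.2-5.2%. Here z/√DE stood in for the frailty test, and the time-by-arm trigger was left out.

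**Step 5: cost of dropping the covariates.** At HR 1.4, power was 75% for log-rank against 81% for adjusted Cox with moderately prognostic covariates, 64% against 77% with strong ones, and no lower with weak ones. Prognostic strength is assumed.

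**The case against.** The strongest reply is that the damage is small. The protocol speaks of a graphical review, so a sensible analyst would ignore trivial crossings; the log-rank test is a valid test of equal curves; the ICC may be far below 0.01; and the word alternative may only mean supplementary. Part of this stands. Ignoring crossings under 2 points on each side roughly halves the false-alarm rate under the null, but still leaves about one trial in two. The Cox result is not expressly discarded, and Primary analysis ties rejection to the Wald test. Replacement is the natural reading, but if a supplement was meant, the text does not say which result decides.

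A reader might infer more than the document supports:
- **That the plan runs at 7-8% type I error.** That holds only if an unclustered log-rank test is always used, with ICC 0.01 and an inferred cluster size.
- **That the switch causes low power under crossing hazards, or that keeping Cox cures it.** Step 3 shows the same weakness in both. A restricted-mean comparison can do better, but the gain depends on the hazard shape assumed.
- **That the wait of up to 4 weeks for specialist assessment makes non-proportional hazards certain.** It makes them possible; the document gives no hazard shapes.
- **That the promise of "comparing the relative mean and median survival times of the two trial arms" is an error because 35-40% stay unresolved.** That is only the conservative sample-size scenario; the other has everyone recovered. The restriction time for a mean is ordinary analysis-plan detail.

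**Conclusion.** The point holds. Curve crossing as written does not diagnose non-proportionality: it occurs by chance in roughly 75-90% of null trials of this design (about 45-60% with a 2-point tolerance), and in about 17-50% at exactly proportional HR 1.4-1.5 when 60-65% resolve, less when nearly all do. The fallback is the score test of the unadjusted Cox model. It does not remedy non-proportional hazards, gives no estimate, and drops the covariates and the physiotherapist frailty.

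The effect on the error rate is modest: about 6-6.7% under the two-stage rule with ICC 0.01 and the inferred cluster sizes, and close to 5% with ICC 0.001. These figures rest on assumed hazard shapes, dropout pattern, cluster size and frailty variance, and the frailty Cox model itself was not fitted. The fault in the trigger and the loss of adjustment do not depend on the clustering assumptions.

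**What to change.** - Delete the curve-crossing criterion and the switch to the log-rank test.
- State that the adjusted frailty Cox Wald test is the single confirmatory test whatever the diagnostics show.
- Assess proportionality with the time-by-arm term.
- If that term indicates non-proportionality, report as supplementary an estimate that does not assume it. Examples are the difference in restricted mean time to resolution to 52 weeks, adjusted for centre, subgroup and pain duration with physiotherapist-clustered standard errors, or hazard ratios by period. Label any log-rank test as supplementary.

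The cost is a few sentences and minor programming, settled before the data are unblinded. The change protects the level of the test and its adjustment; it does not raise confirmatory power if the hazards truly cross.

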#### Process outcomes analysis

Descriptive statistics will be used to examine healthcare resource utilisation by stratification subgroup (subgroups 1, 2, 3) and the number and percentage of participants who proceeded to secondary care treatments, and the types of interventions they received, in both trial arms – and by stratification subgroup (1, 2, 3). Non-parametric tests will be used to test for between-arm comparisons.

#### Internal pilot analysis

Analysis of the internal pilot data will provide information on success of GP practice and physiotherapy site recruitment and retention, recruitment and follow-up rates (over the first 8 months of recruitment), adherence to the treatment protocols, proportion of participants allocated to each of the three subgroups (1, 2, 3), time to ‘fast-track’ MRI and specialist opinion for those in subgroup 3 (‘fast-track’ pathway), the event rate of the primary outcome (recovery) up to 4-month follow-up for all participants (stratified care and control arms) recruited within the 8-month pilot phase in order to check the sample size calculation assumptions. The rate of missing data for the primary outcome will also be checked in the pilot phase for all participants. No formal interim analysis of participants’ clinical outcomes is proposed for the internal pilot.

## Sample size

We have calculated a sample size of 470 participants in total, in order to test for superiority of stratified care compared to non-stratified care. The primary outcome of interest in the SCOPiC trial is time to resolution of symptoms (defined as patient self-report of being ‘completely recovered’ or ‘much better’ compared to baseline (from the 6-point ordinal GPC scale). In our previous trial of stratified care for LBP [23], nearly 60% of patients in total had a clinically important improvement on the GPC scale at 4 and/or 12-month follow up; the absolute difference between arms of that trial at 4 months was 11%. If proportional hazards are to be assumed (i.e. in this case assumed relative rate of ‘resolution’), this difference would equate to an HR in the interval 1.4 - 1.5. Allowing for 20% dropout, a sample size of 470 (235 per treatment arm) is required to detect an HR between 1.4 - 1.5 with 80-90% power (given a two-tailed significance level of 5%), assuming a rate of resolution in excess of 60%, and intra-class correlation (ICC) for physiotherapist effect less than 0.01 (based on estimates from other primary care trials [23, 53], and allowing for a coefficient of variation in physiotherapist cluster size of 0.65 [54]; specifically:an HR of 1.4 in median survival times with 90% power (if all participants in the trial are recovered by 12-month follow-up and ICC for therapist effect is <0.001) (least conservative)an HR of 1.5 in median survival times with 80% power (if 60-65% of participants in the trial are recovered by 12-month follow-up and ICC for physiotherapist effect is 0.01) (most conservative)

An HR above 1 (and correspondingly lower ‘survival’ function) in this context is a positive result in contrast to traditional survival analysis of mortality.

This sample size will also provide more than 80% power to detect a ‘small’ to ‘moderate’ standardised mean difference (effect size) of 0.35 [55] between the two trial arms in a key secondary outcome of physical disability at 12-month follow-up, allowing for an ICC for physiotherapist effect of 0.01.

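### The summary power claim (80-90% for HR 1.4-1.5) and the label on the second worked case overstate power at HR 1.4 when 60-65% resolve; N = 470 and both worked cases are sound

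*Protocol article*

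**What the plan says.** All of this is in the Sample size section of the protocol article.

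- Size and losses: "a sample size of 470 (235 per treatment arm) is required", after "Allowing for 20% dropout".
- Summary claim: this number "is required to detect an HR between 1.4 - 1.5 with 80-90% power (given a two-tailed significance level of 5%), assuming a rate of resolution" above 60%, with a physiotherapist ICC below 0.01 and a coefficient of variation of cluster size of 0.65. The mean cluster size is not given.
- First worked case, labelled *least conservative*: "an HR of 1.4 in median survival times with 90% power (if all participants in the trial are recovered by 12-month follow-up", with ICC below 0.001).
- Second worked case, labelled *most conservative*: "an HR of 1.5 in median survival times with 80% power (if 60-65% of participants in the trial are recovered by 12-month follow-up", with ICC 0.01).

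The HR range is presented as the equivalent of an 11% absolute difference at 4 months in the group's earlier low back pain trial, where nearly 60% of patients improved.

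**The concern.** Between the two cases three things move together: the recovery rate falls from 100% to 60-65%, the ICC rises to 0.01, and the target HR rises from 1.4 to 1.5. The second case is therefore pessimistic on event rate and clustering but uses the easier effect to detect. The combination of HR 1.4 with 60-65% recovery lies inside or at the edge of the bounds in the summary sentence, but no power is given for it.

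This matters because 60-65% recovery is much nearer the document's own evidence than 100% is. The earlier trial had nearly 60% improved, and the Background section cites one-year recovery of 49 to 58% in sciatica (definitions differ between these sources). A reader who takes 80% as the floor could over-read a non-significant result as evidence against an HR of 1.4. For the same reason, an internal pilot event rate pointing to 60-65% could be taken as confirming at least 80% power across the range.

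**Working it through.** **Inputs (Sample size section).** N = 470, 1:1; 20% dropout, so 470 × 0.8 = 376 evaluable; two-sided 5% (z = 1.960); HR 1.4 (ln = 0.3365) and 1.5 (ln = 0.4055); resolution 100% or 60-65%; ICC below 0.001 or 0.01; CV of cluster size 0.65. *Assumption:* mean cluster size m is not stated, so 10-20 patients per physiotherapist is used as a range.

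**Formulas.** Power (Schoenfeld) = Φ(√(events/4) × ln HR − 1.960). Design effect DE = 1 + ((1 + 0.65²)m − 1) × ICC. Effective events = 376 × resolution rate / DE.

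**Step 1: reproduce the plan's two cases.**
- HR 1.4, all recovered: 376 events, √94 × 0.3365 − 1.960 = 1.302, power 90.4% (Freedman 89.8%). Stated: 90%. It reproduces.
- HR 1.5, 60-65% recovered: 376 × 0.60 = 225.6 and 376 × 0.65 = 244.4 events. With no clustering, power is 86.1% and 88.7%. At ICC 0.01, m = 10 gives DE 1.13 and m = 20 gives DE 1.27, so effective events run from 225.6/1.2745 = 177 to 244.4/1.13225 = 216 and power from about 77% to 85%. Stated: 80%. It reproduces for plausible cluster sizes; exactly 80% corresponds to DE 1.18 (60% recovered) to 1.28 (65%).

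**Step 2: change only the HR to 1.4 in the second case.**

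| Setting | Effective events | Power, HR 1.4 |
|---|---|---|
| 60% resolved, ICC 0 | 225.6 | 71.5% (Freedman 70.7%) |
| 65% resolved, ICC 0 | 244.4 | 74.9% (Freedman 74.1%) |
| 60% resolved, ICC 0.01, m = 20 | 177 | 61% |
| 65% resolved, ICC 0.01, m = 10 | 216 | 70% |

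**Step 3: the same question without assuming a cluster size.** If the stated 80% at HR 1.5 is exact, then √(events/4) × ln 1.5 = 1.960 + 0.842 = 2.802. Replacing ln 1.5 by ln 1.4 gives 2.802 × 0.3365/0.4055 − 1.960 = 0.365, so power is 64%. The cluster size cancels, but the result inherits the rounding of the 80%.

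**Step 4: what HR 1.4 would need.** Events for 80% power = 4 × 2.802²/0.3365² ≈ 277, which is 277/376 = 74% resolved with no clustering. With ICC 0.01 it is 277 × 1.132/376 to 277 × 1.2745/376, or about 84-94% resolved for m = 10-20.

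**The case against.** The strongest reply is that no worked figure is wrong. The summary sentence runs straight on into the two cases, which print openly which HR goes with which assumptions. On that reading the first half merely summarises the two pairings and promises nothing about other combinations. The labels follow the bracketed recovery rates and ICCs, and on those two quantities they are correct. This largely stands: a careful reader can see that HR 1.4 is powered only when nearly everyone recovers. It does not fully rescue the text, because one HR range, one power range and one set of bounds are stated together, and *most conservative* implies that nothing less favourable lies within them.

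Three stronger readings are tempting and not supported:

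- *That N = 470 is miscalculated.* Both cases reproduce, so it is not.
- *That power at HR 1.4 simply is 64%.* That figure takes a rounded 80% as exact and sits at ICC 0.01, whereas the summary sentence requires an ICC below 0.01. The range is 61-70% at ICC 0.01 for the assumed cluster sizes, rising to 71-75% as the ICC goes to zero.
- *That a null result will necessarily be misread.* The Primary analysis section reports the HR with a 95% confidence interval, and the Internal pilot analysis section checks the event rate against the sample size assumptions. Both limit the harm.

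One could also apply 60-65% to all 470, giving 282-306 events and 81-84% power for HR 1.4 before clustering. That drops the stated 20% dropout allowance, and matching the stated 80% at HR 1.5 would then require a design effect of about 1.48-1.60.

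**Conclusion.** The point holds as an overstatement in the summary sentence and the label, not as an error in the sample size. With 376 evaluable and 60-65% resolved, power for HR 1.4 stays below 80% at every ICC the sentence allows, including zero, so the shortfall itself needs no assumption about cluster size. It is 5 to 9 percentage points with no clustering (71-75%) and roughly 10 to 19 points at ICC 0.01 (61-70%). The second range rests on the Schoenfeld approximation, the stated CV of 0.65 and the assumed 10-20 patients per physiotherapist. None of this depends on how the HR range of 1.4-1.5 was derived from the earlier trial; the range is taken as given. The point is minor in consequence.

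**What to change.** Keep N = 470 and reword the one paragraph:

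- State 90% power for HR 1.4 only if all participants resolve and the ICC is below 0.001.
- State 80% power for HR 1.5 if 60-65% resolve and the ICC is 0.01.
- Add that HR 1.4 in that second case has about 61-70% power, giving the cluster-size assumption (about 64% given the stated 80% at HR 1.5).
- Say that *most conservative* refers only to event rate and ICC, or drop the label.

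The cost is a less favourable stated power at the lower end of the HR range. No extra participants are needed, and neither conduct nor analysis changes.

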## Economic analysis

The within**-**trial health economic analysis will determine the cost**-**effectiveness of stratified care compared with non**-**stratified care. An incremental cost**-**utility analysis will be undertaken using participants responses to the EQ**-**5D**-**5L questionnaire to calculate the cost per QALY gained. The base**-**case analysis will adopt a health care perspective, incorporating UK NHS and private sciatica-related healthcare resources utilised during the 12-month follow-up period. Analysis from a wider societal perspective will explore the impact on the results when productivity costs are taken into account. Additional exploratory analyses will consider the cost**-**effectiveness of stratified care compared with non-stratified care for participants in each subgroup (subgroups 1, 2 and 3 separately), a strategy used previously in studies of stratified care for LBP [56, 57]. Deterministic and probabilistic sensitivity analyses will be conducted to test the robustness of the results and overall uncertainty in the trial cost and outcome data respectively. Cost-utility planes and acceptability curves will be derived in order to provide a graphical display (plane and curve) and quantification (curve) of the level of uncertainty around incremental cost-effectiveness ratios (ICERs).

## Qualitative analysis

Audio recordings of interviews will be transcribed verbatim, checked and anonymised. Data will be managed and shared using NVivo software, fully coded and analysed thematically [58]. To ensure sufficient data saturation, analysis will follow an iterative process, with topic guides being revised in light of emergent themes. There will be a clearly documented and on-going process of detailed coding, both within and across cases searching for confirmatory and contradictory findings [59]. Data from the patient interviews will also be compared for differences and similarities with the outcome data from the trial [60]. Emerging themes will be explored and discussed at regular trial team meetings which will include clinicians and social scientists. In addition, early findings from the qualitative interviews will be presented to our research user group, which includes individuals who have experienced sciatica symptoms, and their views of the data incorporated into further data collection and analysis.

